# STATISTICS AND ANALYSIS

## Description of Statistical Methods

The analysis will be carried out on the basis of intention-to-treat (ITT). This is, after randomisation, participants will be analysed according to their allocated intervention group irrespective of what they actually receive.

Patient demographic characteristics and other baseline information will be summarised by treatment group. Numbers (with percentages) for binary and categorical variables and mean (standard deviation), or median (interquartile or full range) for continuous variables will be presented. Normality of variables will be assessed by visual assessment of the normality curves and the Shapiro-Wilk test. The analysis of the primary outcome will be assessed using analysis of covariance (ANCOVA) adjusting for baseline values and minimisation factors used in the randomisation process. Results will be presented as adjusted mean difference in change in ambulatory blood pressure between randomised groups at 4 months with 95% confidence intervals (CI) and associated two-sided p value. The analysis of secondary outcomes will also be done using analysis of covariance (ANCOVA) to establish a co-variant model to examine the effect of cardiac structure, vascular function and lifestyle behaviours on exercise capacity. Outcomes measured on more than one occasion will be analysed using a mixed effects model. The data collected from the sub-study will be analysed using paired and independent T-test. If the model assumptions are not met and evidence of departure from Normality is observed, transformations of the data will be employed or non-parametric tests will be carried out. Statistical analysis will be carried out using STATA or SPSS statistical software.

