## The Number of Participants

***Primary Outcome 24-hour awake ambulatory blood pressure***

Our systematic review and meta-analysis of randomised control trials identified an average decrease of 5.4mmHg in systolic blood pressure (SBP) post-intervention via supervised exercise in young adults with prehypertension (mean systolic blood pressure at baseline 126 mmHg). The post intervention standard deviation of change was 8.7 mmHg. Our available cross-sectional pilot data suggests that change will be higher in the preterm born participants and participants exposed to maternal hypertension during pregnancy. To calculate the sample size we have been conservative and used an estimated change of 5 mmHg following 4 months of intervention. We have used a SD of 11.3 from the pooled SD for ambulatory systolic blood pressure from our cross-sectional pilot data. To observe a treatment effect on systolic blood pressure of 5mmHg, powered to 80% (p=0.05) requires a total sample size of 164 participants. The SD deviation for the pooled 24 hour awake diastolic blood pressure is 8.3 mmHg. To observe a treatment effect on diastolic blood pressure of 5mmHg, powered to 80% (p=0.05) requires a total sample size of 114 participants. The power calculations for systolic blood pressure are used to determine the final sample size, with adjustment to 200 participants to allow for 18% attrition. To ensure primary objectives for the study are answered the study team may recruit additional participants to replace those who drop out of the study.

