## Analysis of Outcome Measures

Descriptive statistics (mean, standard deviation, standard error, range, etc) will be calculated for each outcome for each group. Differences in the primary and secondary outcomes will be compared between intervention and control groups.

Mean changes in blood pressures and cardiovascular fitness will be compared across the population and correlated with cardiovascular endpoints including cardiac structure and function reported from cardiac MRI and echocardiogram.

Demographic and physiological characteristics of the participants will be added to regression models as covariates to explore the determinants of change in blood pressure comparing preterm and full term born participants.

Statistical analysis will be carried out using a computer software package, applying statistical methods to analyse dependent and independent variables within the study database. The variable will be plotted to categorize distribution and assess if the data is normally distributed which will guide the statistical methods. Methods such as the Student T-test will assess for differences between the groups and linear regression analysis will be used to assess if the study variables can explain differences in primary outcome. It is hoped that this will then allow for clear understanding on how the cardiovascular system adapts following exercise training and how remodelling may differ according to birth history and early life exposures. For the sub-study, the statistical analysis will be carried out using a computer software package and data will be analysed using paired and independent t-test. This will access the variability of circulating blood biomarkers within the same participant across both visits and also between each participant.

A detailed statistical analysis plan will be written with our statistical team and will be completed before receipt of the data.

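### Observed non-normality may move any outcome, including the primary, from the baseline-adjusted ANCOVA in mmHg to an unspecified transformation or non-parametric test

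*Supplement*

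**What the plan says.** Section 11.1 of the protocol (Description of Statistical Methods) sets the primary analysis as "analysis of covariance (ANCOVA) adjusting for baseline values and minimisation factors used in the randomisation process". It fixes the form of the answer: "Results will be presented as adjusted mean difference in change in ambulatory blood pressure between randomised groups at 4 months", with a 95% confidence interval and an "associated two-sided p value".

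The same section describes one distributional check: "Normality of variables will be assessed by visual assessment of the normality curves and the Shapiro-Wilk test". The fallback follows near the end of the paragraph: "If the model assumptions are not met and evidence of departure from Normality is observed", then "transformations of the data will be employed or non-parametric tests will be carried out". Section 11.3 (Analysis of Outcome Measures) repeats the idea: variables will be plotted to "assess if the data is normally distributed which will guide the statistical methods".

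Neither section names the transformation or the test, gives an order of choice, sets a threshold, says whether baseline adjustment is kept, or exempts the primary outcome. Section 11.3 promises a detailed analysis plan before the data are received. It is not among the documents.

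**The concern.** The first part of Section 11.1 fixes an estimand and the fallback unfixes it. After seeing the data, the analyst could report an adjusted difference in mmHg, a difference on another scale (a ratio, if logs are used), or a rank test with no adjusted mean difference. These answer different questions.

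The described check is also aimed at the variables. ANCOVA does not need a normal outcome or a normal baseline; its distributional assumption concerns the residuals, and with about 80 per arm the adjusted mean difference is robust to moderate non-normality. Eligibility limits the range of baseline awake ambulatory pressure (above 115/75, not above 150/95). The raw baseline values may therefore look non-normal by design, without harm to the model.

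At stake are a primary result whose meaning is fixed in advance and the precision that baseline adjustment buys.

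**Working it through.** **Step 1. Reproduce the planned size.** Inputs from Section 11.2: difference 5 mmHg, SD 11.3, two-sided 0.05, 80% power. The plan states "powered to 80% (p=0.05) requires a total sample size of 164 participants".

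n per arm = 2 × (1.96 + 0.842)² × 11.3² / 5² ≈ 80.2, so 81 per arm and 162 in total (162.3 in total with the t distribution). This agrees with 164 within rounding. Attrition: 164 / 0.82 = 200, as stated. The calculation takes no credit for baseline adjustment.

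**Step 2. Precision bought by adjustment, from eTable 3 (per-protocol, 16 weeks).** Adjusted SE = CI width / (2 × 1.96). Unadjusted SE = √(SD₁²/n₁ + SD₂²/n₂).

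| | Unadjusted SE | Adjusted SE | Variance ratio |
|---|---|---|---|
| Systolic | √(11.58²/71 + 10.00²/84) = 1.755 | (2.92 + 2.87)/3.92 = 1.477 | 0.709 |
| Diastolic | √(7.04²/71 + 6.73²/84) = 1.112 | (2.64 + 1.41)/3.92 = 1.033 | 0.863 |

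The systolic ratio corresponds to a baseline correlation of √(1 − 0.709) = 0.54.

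**Step 3. Correlation implied by the planning SDs.** Section 11.2 gives an SD of 11.3 and an SD of change of 8.7. If both described the same population with equal variances (an assumption), correlation = 1 − 8.7² / (2 × 11.3²) = 0.70, and the variance ratio would be 1 − 0.70² ≈ 0.505 (unrounded correlation 0.7036).

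**Step 4. Information lost by an unadjusted rank test of 16-week values, relative to ANCOVA.** On normal data a rank test has efficiency 3/π = 0.955 against the t-test, so loss = 1 − 0.955 × variance ratio.

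| Basis | Loss from dropping adjustment | Loss including rank factor |
|---|---|---|
| Systolic, eTable 3 | 29% | 32% |
| Diastolic, eTable 3 | 14% | 18% |
| Planning SDs | 50% | 52% |

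Most of the loss comes from dropping the adjustment. The 0.955 factor belongs to normal data; with clear skew the rank component could be smaller or reverse.

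**Step 5. Power for 5 mmHg at 82 per arm, SD 11.3** (simulation, normal data, 4,000 runs):

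| Analysis | Correlation 0.54 | Correlation 0.70 |
|---|---|---|
| ANCOVA in mmHg | 92% | 98% |
| ANCOVA on log values | 92% | 97% |
| Rank ANCOVA (baseline kept) | 90% | 97% |
| Rank test on change | 82% | 94% |
| Rank test on 16-week values | 79% | 79% |

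The cost depends on which fallback is chosen, and the protocol leaves that open.

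**The case against.** The strongest reply has four parts.

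- **The trigger is narrower than a significance test.** Shapiro-Wilk is paired with visual assessment, and the fallback also needs model assumptions to be unmet, which would ordinarily bring in residuals. This stands: a reader might infer that a failed Shapiro-Wilk test alone displaces ANCOVA, and the text does not say so. But normality of variables is the only check described, so the second condition supplies no defined gate.
- **The fallback need not cost much.** A transformation keeps the adjusted model, and adjusted rank methods are not excluded. This also stands. It would be wrong to say that either fallback discards about a third of the information; that figure belongs to one permitted option and one outcome. The transformation still loses the promised mmHg difference.
- **Planned power is not threatened.** The trial was sized for an unadjusted comparison, and the unadjusted rank test reaches about 79% against 80%. This stands. Nor is any inflation of the type I error shown.
- **The detail belongs to the analysis plan.** Names and thresholds could be left there. But the protocol does more than stay silent: it states, in two sections, that the distribution steers the method. A later plan may override that, but the wording needs correcting.

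The results shown are baseline-adjusted and in mmHg (eTables 2 and 3), so nothing indicates that the primary analysis was in fact replaced. The point concerns what the plan allows.

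**Conclusion.** The point holds as a cheap improvement. Section 11.1, echoed in Section 11.3, lets the observed distribution change the method for the primary outcome without saying to what.

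The size depends on the fallback. A transformation costs almost no power but changes the scale. An unadjusted rank test of 16-week values loses about 32% of the information for systolic and 18% for diastolic pressure. Those two figures are approximate: they come from a per-protocol mixed model that also adjusts for minimisation factors. The planning SDs give about 52%, which rests on an implied correlation of 0.70 that the protocol never states. Power falls from about 92% (correlation 0.54, assumed) to about 79%.

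The loss is thus mainly of a fixed estimand and of precision above the planned 80%. The documents do not support a claim that the trial would be underpowered or its error rate inflated.

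**What to change.** Replace the fallback sentence in Section 11.1, align Section 11.3, and carry the wording into the analysis plan:

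- The ANCOVA or mixed model in mmHg, adjusted for baseline and minimisation factors, is the primary analysis whatever a normality test shows.
- Model checks use residual plots, not tests on raw variables.
- If residuals are clearly non-normal, add a bootstrap or heteroscedasticity-robust interval for the same adjusted difference.
- Any transformed or rank-based analysis of the primary outcome is a sensitivity analysis.
- Biomarkers to be log-transformed are named in advance.

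The cost is about one paragraph of text and a little extra analysis work. Sample size and data collection do not change.

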## The Number of Participants

***Primary Outcome 24-hour awake ambulatory blood pressure***

Our systematic review and meta-analysis of randomised control trials identified an average decrease of 5.4mmHg in systolic blood pressure (SBP) post-intervention via supervised exercise in young adults with prehypertension (mean systolic blood pressure at baseline 126 mmHg). The post intervention standard deviation of change was 8.7 mmHg. Our available cross-sectional pilot data suggests that change will be higher in the preterm born participants and participants exposed to maternal hypertension during pregnancy. To calculate the sample size we have been conservative and used an estimated change of 5 mmHg following 4 months of intervention. We have used a SD of 11.3 from the pooled SD for ambulatory systolic blood pressure from our cross-sectional pilot data. To observe a treatment effect on systolic blood pressure of 5mmHg, powered to 80% (p=0.05) requires a total sample size of 164 participants. The SD deviation for the pooled 24 hour awake diastolic blood pressure is 8.3 mmHg. To observe a treatment effect on diastolic blood pressure of 5mmHg, powered to 80% (p=0.05) requires a total sample size of 114 participants. The power calculations for systolic blood pressure are used to determine the final sample size, with adjustment to 200 participants to allow for 18% attrition. To ensure primary objectives for the study are answered the study team may recruit additional participants to replace those who drop out of the study.

***Secondary Outcome Measures***

*Angiogenesis*

*We have previously reported differences in angiogenic factors between preterm and full term participants* (S-Eng preterm 5.64± 1.03 vs control 4.06±0.85 ng/mL). 90% power to observe the same differences will be achieved with at least 10 participants per group. The sample size will be powered to over 80% to observe a 10% change in S-Eng in the preterm and full term participants^9^.

*Microvascular Measures*

*Retinal vasculature*

Hanssen *et al* demonstrated a 6% improvement in arteriolar to venular diameter ratio (AVR) increasing from 0.81 (SD 0.05) to 0.86 (SD 0.1) after 10 weeks aerobic exercise in young healthy males[^43^](#_ENREF_43). To replicate this would require a minimum of 40 participants in the training group and 40 participants in the control group. The sample size of 200 participants is powered to detect a 5% change in retinal imaging parameters.

*Angiogenesis*

*We have previously reported differences in angiogenic factors between preterm and full term participants* (S-Eng preterm 5.64± 1.03 vs control 4.06±0.85 ng/mL). 90% power to observe the same differences will be achieved with at least 10 participants per group. The sample size will be powered to over 80% to observe a 10% change in S-Eng in the preterm and full term participants^9^.

MRI Imaging

MR imaging will be performed on half of the participants in each group. In order to avoid selection bias, all study candidates shall be asked if they would like to take part in MR imaging as a standard component of the consent process. All study participants who volunteer and consent for MR imaging and are not contraindicated to MR scanning, shall be offered a place in their MR imaging sub-group until all places are filled. If there are multiple consented volunteers for the last slot, it shall be offered according to participant consent date (earliest to latest) until the place is filled.

*MRI sub-group Cardiac Measures*

50 participants/group provides 85% power to identify 10% change in LVM index (young adult preterm LVMi 66.5+/-10.9 g/m2) and 80% power to observe a change of 7% in end-diastolic volume (mean EDV 72.2+/-9.3ml) and 12% in longitudinal ventricular strain^14,15^.

*MRI sub-group Cerebrovascular Measures*

White matter integrity

In children and adolescents, maintaining high cardiovascular fitness can be associated with between 5% and 10% difference in regional FA[^42^](#_ENREF_42). In older adults, the difference in regional FA between sedentary groups and those that maintain light to moderate activity is between 1 to 2%. With 100 participants in the MRI study, the intervention will be powered to 80% to report between 4% and 7% change between training and control groups.

*Small vessel tortuosity*

Maintaining higher cardiovascular fitness is associated with over a 15% difference in vessel tortuosity compared to lower fitness in older adults[^32^](#_ENREF_32). The study will be powered to 80% to detect 1% improvement in vessel tortuosity in the exercising participants with 100 participants completing MRI imaging (50 training).

Cerebrovascular Perfusion

Mersov et al in a modelling estimation of the sample size required to detect an arterial spin labelling magnetic resonance imaging perfusion abnormality in voxel-wise group analyses^52^ identified a requirement for a minimum of 22 participants for a 15% difference and 37 participants for a more modest 10% difference.

*Structural volumes*

Grey matter volumes are reduced in preterm born adolescents and young adults compared to full born controls. Mullen *et al* report preterm volumes of 659.3 cm3 (SD 52) compared to 700 cm3 (SD 51)[^42^](#_ENREF_42). This study will be powered to detect 6% improvement in preterm grey matter volumes equivalent to increasing volumes to mean values in the full term population

*Blood validation sub-study*

To validate methodology and assess variability a minimum number of 12 participants are needed as recommended for pilot investigations^53^.

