Study visits 1 & 2 will take approximately 3 hours for core study measures while visit 3 will take approximately 1.5 hours. Participants completing the MRI sub-study will complete an additional 90 minutes of MRI imaging within one week of their primary trial visit.

Core study measures will include echocardiogram for measures of cardiac structure and function, microvascular assessment with retinal imaging and dermal capillaroscopy, cardiopulmonary exercise testing (CPET) for fitness assessment, and resting and post exercise blood samples to measure inflammatory, angiogenic, vasoactive and metabolic profiles. A subgroup of study participant (n=100, 50 control and 50 intervention participants) will complete detailed MRI imaging including liver, cardiac and brain imaging.

In advance of the study visit participants will be invited to complete an online study questionnaire. The questionnaire will record correlates of physical activity behaviour and self-reported lifestyle behaviours such as smoking and alcohol consumption. Lifestyle behaviours are important determinants and risk factors for the development of elevated blood pressure and cardiovascular risk.

The study visit will conclude with participants being fitted with physical activity and 24 hour blood pressure monitors (if the baseline visit occurs within 30 days of the screening visit, a 24 hour blood pressure monitor will not be fitted at that time). Participants will be asked to wear the wrist worn activity monitors for 7 days. Participants will return monitoring devices using prepaid envelopes. If monitors are not returned after 2 weeks, the study team will give the participants a telephone call to ask for the devices to be returned. Compliance with returning self-monitoring devices in previous and ongoing ethically approved studies run by our group has been high. When the devices are returned, this will represent completion of the primary activities of the trial visit.

To test the reproducibility of the blood cell and circulating biomarkers, participants will be asked to fast for four hours prior to blood sampling but encouraged to continue drinking water. Up to 30mL of venous blood will be taken at visit 1 and again at a follow-up visit (visit 2), which will be exactly one week after visit 1. Blood samples processing, storage and experiments will be conducted as for the main TEPHRA study.

A flowchart for the planned study procedures can be found in appendix C at the end of this protocol.

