**MRI Subgroup Measures**

Subgroup [n=100, including up to 50 preterm born participants and up to 50 full term born participants]

Participants in the MRI subgroup will complete MRI imaging of the Brain, Liver and Heart. Imaging will be completed at the Oxford Centre of Magnetic Resonance. For participants in this subgroup, study visits will commence with image acquisition.

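### Section 11.2 credits a 7% change in end-diastolic volume with 80% power; the basis that reproduces the LV mass figure in the same sentence gives about 77%, and neither cardiac MRI figure states an allowance for lost scans

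*Supplement*

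**What the plan says.** Section 11.2 (The Number of Participants), under the cardiac measures of the MRI sub-group, gives two checkable power statements in one sentence.

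- LV mass index: "50 participants/group provides 85% power to identify 10% change in LVM index (young adult preterm LVMi 66.5+/-10.9 g/m2".
- EDV: "80% power to observe a change of 7% in end-diastolic volume (mean EDV 72.2+/-9.3ml".

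The sentence names no test, significance level, sidedness or attrition allowance. Section 6 (Trial Design) fixes the size of the sub-group by arm: "n=100, 50 control and 50 intervention participants". Section 5 schedules cardiac MRI at baseline and again at the end of the 16-week intervention.

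For the primary outcome, section 11.2 works differently. It derives 164 participants and then enlarges the number, "with adjustment to 200 participants to allow for 18% attrition".

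**The concern.** The two cardiac figures share a sentence, a group size and a form of input (mean, SD, percentage change), so one calculation should give both. It gives the LV mass figure but not the EDV figure, and the EDV error is in the favourable direction.

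The statement is also made for 50 per group, which is the whole planned sub-group. A participant contributes to a baseline-to-16-week comparison only with both scans. The sample size section expects loss for the primary outcome but does not say whether the MRI figures are for participants scanned or for participants with both scans. A reader who later weighs a non-significant EDV or LV mass result against these powers could take it as stronger evidence of no effect than the stated inputs allow.

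**Working it through.** **Inputs, all from section 11.2 unless stated**

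- EDV: mean 72.2, SD 9.3, change 7%. Difference = 0.07 × 72.2 = 5.054 ml; d = 5.054 / 9.3 = 0.543.
- LV mass index: mean 66.5, SD 10.9, change 10%. Difference = 0.10 × 66.5 = 6.65 g/m²; d = 6.65 / 10.9 = 0.610.
- n = 50 per group.
- Alpha = 0.05 two-sided. This is assumed for the MRI figures: section 11.2 gives 0.05 for the primary outcome, and section 11.1 specifies a two-sided p value for it.

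**Formula.** Two independent groups, no baseline adjustment. Normal approximation: power = Φ(d·√(n/2) − 1.960). The noncentral t gives slightly lower values.

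**Step 1: reproduce the LV mass figure.** At n = 50, √(n/2) = 5. Then 0.610 × 5 − 1.960 = 1.090, and Φ(1.090) = 86.2%. The t-test gives 85.6%. The printed 85% is reproduced.

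**Step 2: apply the same test to EDV.** 0.543 × 5 − 1.960 = 0.757, and Φ(0.757) = 77.6%. The t-test gives 76.7%. The printed 80% is not reproduced; the gap is 2.4 to 3.3 points.

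**Step 3: look for a reading that gives 80%.**

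- One-sided 5%: 85 to 86%. No match.
- Within-group paired test with n = 50 (correlation 0.5): 96%. No match.
- Difference detectable with 80% power at 50 per group (t-test): d = 0.566, so 0.566 × 9.3 / 72.2 = 7.3%. The normal formula gives 7.2%. Rounded to a whole percent this is 7%, the likely origin of the printed pair.
- Group size needed for 80% power at exactly 7%: 54.1 by the t-test, so 55 per group.

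**Step 4: the effect of loss.** The primary calculation has the same unadjusted form. With 5 mmHg and SD 11.3, the normal formula gives 2 × (1.960 + 0.842)² × (11.3/5)² = 80.2, so 81 per group or 162 in total, against the printed 164; then 164 / 0.82 = 200. If the same 18% were lost from the MRI sub-group, 50 × 0.82 = 41 per arm would have both scans. Applying this rate to MRI is an assumption.

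| Unadjusted t-test, two-sided 5% | 50 per arm | 41 per arm | Change with 80% power at 41 |
|---|---|---|---|
| EDV, 7% | 76.7% | 68.1% | 0.626 × 9.3 / 72.2 = 8.1% |
| LV mass index, 10% | 85.6% | 77.9% | 0.626 × 10.9 / 66.5 = 10.3% |

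**Step 5: the effect of baseline adjustment.** With ANCOVA the residual SD is SD × √(1 − r²), where r is the correlation between baseline and follow-up. The documents give no r for any MRI measure, so the table shows a range.

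| Assumed r | EDV, 50 per arm | EDV, 41 per arm | LV mass, 41 per arm |
|---|---|---|---|
| 0 | 76.7% | 68.1% | 77.9% |
| 0.3 | 80.5% | 72.2% | 81.6% |
| 0.5 | 87.4% | 80.1% | 88.3% |
| 0.7 | 96.5% | 92.6% | 96.9% |

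EDV reaches 80% at r of about 0.28 with 50 per arm and about 0.50 with 41. LV mass regains 85% with 41 per arm at r of about 0.41.

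**The case against.** The strongest reply has four parts.

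- **Rounding.** The effects in the sentence are whole percents, and a detectable change of 7.2 to 7.3% would be printed as 7%. This is probably what happened. It explains the figure, but the printed pair of 7% and 80% still does not fit its inputs.
- **Planned analysis.** Section 11.1 names ANCOVA for secondary outcomes and a mixed model for repeated measures, and a modest correlation restores 80%. This stands as a reason not to claim a proven shortfall. However, the ANCOVA for secondary outcomes is described there as a model for exercise capacity, section 11.3 names the t-test for group differences, no correlation is given, and the LV mass figure reproduces without any adjustment. The stated powers therefore do not appear to rest on baseline adjustment.
- **Attrition.** The 18% is applied only to the primary outcome. Sections 8.9 and 11.2 allow withdrawn participants to be replaced, and the vessel tortuosity figure is worded for participants who complete imaging. So 41 per arm is an illustration and not a figure from the plan. Replacement is optional, though, and nothing says that the MRI place of a participant who drops out is reopened. The cardiac sentence does not say that it counts only those with both scans.
- **Consequence.** The trial is sized on systolic blood pressure, and nothing says that null MRI results will be judged against these powers. This keeps the point minor.

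**Conclusion.** The EDV statement is wrong on the basis that reproduces its neighbour: about 77% power for a 7% change at 50 per group, or 80% for about 7.3%. The LV mass statement is right for 50 participants per group with both scans. Neither figure states an allowance for loss between scans. At 41 per arm, unadjusted power would be about 68% for EDV and 78% for LV mass, if the 18% loss assumed for the primary outcome also applied here and no baseline adjustment were used.

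A reader might infer that the MRI power statements fail as a whole. The documents do not support that. The strain, fractional anisotropy and tortuosity figures come without an SD and cannot be checked. The perfusion minimum of 22 or 37 participants would still be met by the 82 left after 18% loss. The grey-matter statement, "This study will be powered to detect 6% improvement in preterm grey matter volumes", gives no power that could be missed, and no split of preterm MRI participants by arm is stated. Nor can it be said that the sub-study has only 68% power for EDV: the unstated correlation leaves both a shortfall and adequate power possible under a baseline-adjusted analysis.

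This is a minor correction to a secondary sub-study.

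**What to change.** In section 11.2, MRI sub-group cardiac measures:

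1. Correct the EDV statement to 77% power for a 7% change, or 80% for a 7.3% change, at 50 evaluable participants per arm.
2. Name the test, significance level and sidedness, and say that the cardiac figures are for participants with both the baseline and the 16-week scan.
3. Add the unadjusted power at 41 per arm, labelled as assuming the 18% loss used for the primary outcome: 68% for EDV at 7% (80% at 8.1%) and 78% for LV mass at 10% (80% at 10.3%).
4. If baseline-adjusted ANCOVA is the intended basis, give the assumed correlation and the power that follows from it, in place of or beside the unadjusted figures.

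The cost is a few restated figures, slightly less favourable than those printed. No additional scans or participants are needed.
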